### Isolating the peripheral blood mononuclear cells (PBMCs) and metabolomic analysis

A random subsample of participants (20 subjects in each group, *n*=40) will be included to isolate the PBMCs by Ficoll gradient, as previously described [41]. The following fluorochrome-conjugated antibodies will be used: CD4, CD8, PD1, CD62L, KLRG1, CD28, CD57, CD163, CD119, CD56, CD116, CD66b, CD11b, and CD14. Cells will be washed, stained and analyzed by flow cytometry. In addition, plasma lipid extraction will be performed and then analyzed by ultrahigh-resolution liquid chromatography coupled to mass spectrometry (UHPLC–MS) using ultrahigh-resolution liquid chromatography coupled to mass spectrometry (UHPLC–MS) using the technique described by Barr et al. [42]. In summary, plasma lipid extraction is a liquid extraction of the serum with chloroform/methanol (2:1) and a saline solution of sodium chloride followed by incubation the mixture for 1 h at −20 °C to promote the precipitation of proteins. Next, the sample is evaporated in an evaporating concentrator, and the dry extract is reconstituted in acetonitrile/isopropanol. After centrifugation, the supernatant is analyzed by UHPLC–MS. For this purpose, the chromatographic column UPLC BEH C18, 2. 1×100 mm, 1.7 μm (Waters Corp. Milford, MA, USA) will be used, with a mobile phase consisting of a binary mixture formed by H_2_O/acetonitrile/10 mM ammonium formate and acetonitrile/isopropanol/10 mM ammonium formate. The conditions of chromatographic separation and high-resolution mass spectrometry (Xevo G2 QToF, Waters Corp.) have been previously described [43].

### Resting energy expenditure

The resting energy expenditure (REE) will be measured using an automated metabolic gas analysis system (Q-NRG+ COSMED Rome, Italy). Participants will be instructed to lie in a supine position while enclosed in a clear hard plastic canopy, which is attached to the metabolic cart and dilution pump via a breathing tube. To do this, patients will lie down for 5–10 min. V̇O_2_ and carbon dioxide production (V̇CO_2_) will be measured for 30 min. Measurements will be taken first thing in the morning after fasting for 10 to 12 h, without smoking or consuming alcoholic beverages, and before performing any physical activity or personal hygiene. To avoid possible measurement biases and to decrease the variability between subjects, controls and calibrations of the CO_2_ and environmental thermoneutrality (temperature between 20 and 24 °C) will be carried out before each test, as indicated by the manufacturer. Additionally, weekly self-calibrations will be performed using a standard gas mixture of 95% O_2_ and 5% CO_2_. As recommended by the manufacturer, a nonprotein stoichiometric equation will be used to estimate the resting fat oxidation rate = (1.695 × V̇O_2_–1.701 × V̇CO_2_) [44].

### Anthropometrics and body composition

Participants will be tested wearing minimal clothing and barefoot. Height will be measured to the nearest 0.1 cm with a portable stadiometer (Seca 206, Seca Ltd, Birmingham, UK). Body mass will be determined to the nearest 0.1 kg using a calibrated scale (Seca HV120, Seca Ltd, Birmingham, UK) with the participant in light clothing. Body mass index will be calculated as body mass (kg) divided by height squared (m^2^). DXA will be used to assess, lean mass (kg), total body fat (%), bone mineral density (g/cm2), abdominal adiposity (g), truncal adiposity (g), and limb adiposity (g) (Lunar Prodigy, GE Healthcare, Madison, Wisconsin, USA; enCORE V.14.10.022).

### Blood pressure, vascular stiffness, and heart rate variability

Blood pressure will be assessed using a VaSera VS-2000 device (Fukuda Denshi, Japan). Participants will be asked to rest for 5 min before 5 blood pressure and heart rate readings will be taken at 2-min intervals by a trained study investigator. Pulse wave velocity (PWV) and cardio-ankle vascular index (CAVI) will be estimated by brachial-ankle oscillometry using a VaSera VS-2000 device (Fukuda Denshi, Japan) as markers of vascular stiffness according to Shirai et al. [45]. For each patient, a single determination will be used to determine the systolic and central and peripheral diastolic blood pressure variables, the CAVI index, and PWV with the participant resting supine for at least 10 min before the measurement. Electrocardiogram electrodes will be placed on both wrists, a microphone for detecting heart sounds will be placed on the sternum, and cuffs will be wrapped around both upper arms and above each ankle.

Heart rate variability (HRV) will be measured by the cardiofrequency meter Polar® Vantage V2™ (Polar Electro Oy, Kempele, Finland). This system captures the R wave of the ECG with a sampling frequency of 500 Hz, thus calculating the HR instantly. Low frequency (LF, 0.04–0.15 Hz), high frequency (HF, 0.15–0.4 Hz), and very low frequency (VLF, 0.0033–0.04 Hz) are different frequencies with varying power ranges. The ratio of LF to HF (LF/HF, %) is used to quantify the degree of sympathetic and parasympathetic balance in the body. In addition, the time domains measured in this study, including root mean square of successive RR interval differences (RMSSD) and the standard deviation of NN intervals (SDNN), will be reported as milliseconds (ms).

### Health-related quality of life and cognitive function and mental health

The Spanish version of the EuroQOL EQ-5D instrument [46] (concordance correlation coefficient: 0.948) will be used to assess health-related quality of life (HRQoL). The EQ-5D-5L was selected because it is an easy-to-use tool with adequate psychometric properties and can produce a single HRQoL index. In recent years, its use has been extended to general outpatient and in-hospital clinical research, which is consistent with the collection of HRQoL information for patients in the referral program [47]. In addition, the EuroQol visual analog scale will be used to ask patients to score their quality of life from 0 (worst imaginable health) to 100 (best imaginable health) before COVID-19 and at the time of the visit. *Cognitive function* will be measured by the Montreal Cognitive Assessment (MOCA) [48] (Cronbach’s *α* = 0.886) is a performance test that is used to screen for cognitive impairment. The score ranges from 0 to 30 points, with higher scores indicating better cognitive performance. A score ≤ 24 indicates cognitive impairment [49]. The Trail Making Test A [50] (reliability at least 0.76 for Part A) will be used to evaluate attention. For mood, participants will be evaluated via the brief Spanish version of the Community Epidemiological Study-Depression scale (CES-D), a 10-item self-report concerning the past week. The CES-D short form has shown high reliability and internal consistency [50] and validity for the identification of depressive symptoms [51]. Possible scores range from 0 to 30, with higher scores reflecting more severe depressive symptoms. To identify patients with probable clinical depression, we will use the recommended cutoff of 10 [51].

*Psychological distress* will be evaluated with the 10-item Kessler Psychological Distress scale (K10), which is a self-report instrument for the detection of nonspecific psychological distress. This scale has strong psychometric properties and is able to discriminate psychiatric cases from noncases [52, 53]. The K10 consists of 10 items with each five Likert-type response categories: “none of the time” (1), “a little of the time” (2), “some of the time” (3), “most of the time” (4), and “all of the time” (5). Sum scores range from 10 to 50, with higher scores indicating more symptoms or more frequent experience of those symptoms. *Resilience* will be measured by the Brief Resilient Coping Scale (BRCS), which is a 6-item measure designed to capture tendencies to cope with stress in a highly adaptive manner (internal consistency *α*=0.76, and test-retest reliability *r* = 0.71) [54]. Resilient coping is conceptualized as coping with stress in a highly adaptive manner, using a 5-point Likert scale “from ‘1’ = describes me not at all to ‘5’ = describes me very well.” Higher scores indicate that the individual perceives they have a better ability to “bounce back” and recover from stressful events and/or situations. *The chronic burden ongoing* (i.e., lasting for 7 weeks or longer) strains will be assessed in four domains: health of close others, work, finances, and relationships [55]. Respondents will be asked to indicate whether (yes, no) they are experiencing an ongoing problem in each of these domains and, if so, to indicate how stressful the ongoing problem is. We will sum the number of domains for which the respondent reports experiencing moderately stressful or very stressful ongoing problems (range, 0–4; 0 = no, 2 = yes, not very, 3 = yes, moderately, and 4 = yes, very stressful). We will also measure *life satisfaction* using one question: using a scale from 0 to 10 where 0 means “the worst possible life overall” and 10 means “the best possible life overall,” how would you rate your life overall these days? [56]. Last, *stress perception* will be measured by the 1 Item Statistics Canada Stress Question (SCSQ) with a possible score of 0 to 10, where higher scores indicate more stress.

### Questionnaire on sociodemographic and health-related data

The following data will be recorded in a standardized questionnaire by the staff researcher at baseline: sociodemographic data (age, sex, marital status, highest educational level, employment status, monthly income), risk factors (sleeping habits, eating habits, alcohol consumption, diet, physical activity levels), and health-related data (vaccines, self-reported diseases, medications, illness in family history).

### Safety group and assignment of possible events

The research team will consist of professionals from the health sciences and physical activity sciences, physical therapists, and rehabilitators with experience in cardiovascular management and safety in the clinical and primary care settings. Training, coaching, and standardization in the measurement of variables, programs, record sheets, and databases will take place. Additionally, the study will gather a group of specialists with experience in the management of exercise interventions (internal medicine) in accordance with the recommendations of the Tripartite Guide of the International Conference on Harmonized Good Clinical Practices to provide support and safety in case of possible adverse events. Study staff will collect data on spontaneously reported adverse events. Severe adverse events will be promptly reported to the Regional Ethics Committee of the HUN in accordance with the recommendations of the GBPC. Management of adverse effects will be based on participant protection and safety. The following adverse events will be recorded: signs of infections, hospital admissions, angina pectoris, and injuries/pain that prevent participation in training. Any serious adverse events (death, life-threatening event, hospital admission, expected or unexpected) will be reported to the Regional Ethics Committee of the HUN in accordance with the recommendations of the GBPC within 7 days after the study principal investigator or physician has become aware of the occurrence. These reports will include (a) recruitment and follow-up in terms of person-days and in comparison with the preestablished goals; (b) participant adherence (in terms of biochemical markers and data on the degree of compliance) and comparisons with the expected objectives of the exercise groups; (c) quality control (preferences for certain digits, variability, out-of-range values); and (d) intermediate and final variables and primary and secondary outcomes for each group and comparisons between groups with respect to the primary and secondary variables. A telephone number and email address will be made available to allow the monitors to make inquiries and resolve doubts. The program monitors will prepare a report on the participants’ attendance and, where appropriate, the possible reasons for drop out.

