### Objectives

The primary objective of this study is to compare the effects of 6 weeks of RT vs. standard care on the clinical status of patients with persistent COVID-19 symptoms. Changes in clinical status will be determined by examining changes in perceived persistent symptoms (i.e., fatigue/tiredness, musculoskeletal pain, shortness of breath). In addition, the secondary objective of this study is to compare the effects of RT on measures of immunological and inflammatory markers, cardiovascular health, and psychosocial responses to exercise. Changes in immunological and inflammatory markers will be measured by assessing lymphocyte immunophenotypes and cytokine assays. Changes in cardiovascular health will be measured by assessing resting blood pressure, arterial stiffness, heart rate variability, maximal aerobic capacity (V̇O_2_max), muscle strength, and body composition. Psychosocial responses to exercise will examine the effect of RT on perceived persistent symptoms (i.e., fatigue/tiredness, musculoskeletal pain, shortness of breath) in response to the exercise intervention. The RT exercise intervention will be conducted using a whole-body paradigm, which will utilize Smart Strength machines (eGym® GmbH, München, Germany) and cycle ergometer.

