### Participant eligibility

A total of 100 adults of both sexes between 20 and 60 years old will be recruited from the Hospital Universitario de Navarra (HUN). At the HUN site, participants will be admitted from internal medicine service referrals and from participant databanks of patients who have consented to be contacted for participation in research projects. All patients will be screened for inclusion by a physician to ensure that the patient has been diagnosed with COVID-19 and has no other psychiatric or somatic condition that can explain the persistent COVID-19 symptoms. Potential participants will fulfill the following inclusion criteria: over 18 years of age, diagnosed with SARS-CoV-2 using real-time reverse transcriptase polymerase chain reaction (PCR) tests or testing positive for SARS-CoV-2 virus antigen >90 days before randomization, presenting with a chronic symptomatic phase lasting >90 days since the onset of symptoms, has not been hospitalized, has no evidence on clinical records of pneumonia or any other organ failure related to SARS-CoV-2, and is capable and willing to provide informed consent. Patients previously treated for persistent COVID-19 symptoms (i.e., physical therapy or rehabilitation); patients who are pregnant or breast-feeding; patients with cardiovascular or endocrine comorbidities (i.e., atrial fibrillation, acute myocarditis, acute heart attack or unstable angina, aortic stenosis, acute endocarditis/pericarditis, uncontrolled high blood pressure, acute thromboembolism, severe heart failure, respiratory failure, and uncontrolled acute decompensated diabetes mellitus or low blood sugar) or other neurological or musculoskeletal comorbidities that will prevent safe exercise participation; patients with pain that is made worse with exercise; patients with cognitive, communication, or behavioral issues that may limit their safe participation in the exercise program, or contraindications that will prevent their participation in the exercise intervention; and patients who have been treated with IL-6 receptor antagonists (tocilizumab, kevzara) within the last month, due to drug interference with the cardiopulmonary exercise adaptations, will be excluded.

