**Fig. 2 Fig2:**
[figure not shown]
Flow of subjects through the “EXER-COVID Crossover Study”. Participants will be first randomly assigned to a 6-week period of no-exercise training (Sequence 1, *n*=50) or exercise training (Sequence 2, *n*=50) after which full crossover occurred. T: time-point; PROMs: patient-reported outcome measures; REE: resting energy expenditure; HRV: heart rate variability; BP: blood pressure

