### Intervention

All interventions will take place at the Biomedical Research Center of Navarra (Navarrabiomed) site facilities. Standard medical care will be provided to all participants in all groups. The exercise intervention will consist of 6 weeks of individualized supervised muscle power RT, two sessions per week performed on nonconsecutive days to avoid overtraining and maximize adaptations. To reduce the risk of COVID-19 reinfection, a 1:1 trainer-to-participant format will be used during training sessions. On the training days, the participants will warm up with 3 sets of 10 repetitions of half air squats with the participants’ own body weight followed by 10 min on an electronically braked cycle ergometer (Lode Excalibur Sport, Groningen, The Netherlands) at 50% of the VO_2_peak and 4 sets of 30 s followed by 90 s of passive recovery at 100–120% of the VO_2_peak. EGYM Smart Strength machines (eGym® GmbH, München, Germany) will be used for both RT and maximum strength and muscle power measurements of the lower and upper extremity muscles. Muscle power RT, including motivational gamification and maximum acceleration of constant weight from 50 to 70% of daily maximum strength measurements, will be used during training (Explonic eGym® intelligent training program).

The RT intervention will comprise 3 sets of 8 to 12 repetitions with a load equivalent to 50 to 70% of the daily 1-repetition maximum (1 RM) for all major muscle groups (i.e., the exercises for the upper body include pectoral press and back press, and the exercises for the lower body include leg press and leg extensions). All movements will be performed at 100% of the maximum speed achieved during the propulsive phase (i.e., as fast as possible according to the patient’s muscular and functional capacity). The recovery between sets will be between 1 and 2 min. At the end of the session, there will be 5 min of stretching to cool down. The duration of the sessions will be 30–45 min, and the duration of the entire program will be 6 weeks, equivalent to 12 sessions. See Table 1 for details.

**Table 1 Tab1:** Supervised exercise program for “EXER-COVID Crossover Study”

Weeks	1		2		3		4		5		6	
***Session***	***1***	***2***	***3***	***4***	***5***	***6***	***7***	***8***	***9***	***10***	***11***	***12***
Warm up	3 sets of 10 reps of bodyweight half squat+ 10 min at cycling at 50% of V̇O_2_peak+4 sets of 30 s at 100–120% of V̇O_2_peak											
Strength training												

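### Worsening of fatigue or breathlessness is not a named adverse event, and spontaneous reporting gives the two conditions unequal opportunity to report it

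*Protocol article*

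**What the plan says.** The safety section of the protocol article gives a method of collection and a list. The method is passive: "Study staff will collect data on spontaneously reported adverse events". The list has four kinds of event: "The following adverse events will be recorded: signs of infections, hospital admissions, angina pectoris, and injuries/pain that prevent participation in training".

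The Objectives section names the symptoms on which the trial intends to show benefit: "Changes in clinical status will be determined by examining changes in perceived persistent symptoms (i.e., fatigue/tiredness, musculoskeletal pain, shortness of breath"). Under Participant eligibility, everyone enters "presenting with a chronic symptomatic phase lasting >90 days since the onset of symptoms".

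The Intervention section describes close contact during exercise: "a 1:1 trainer-to-participant format will be used during training sessions", and "the duration of the entire program will be 6 weeks, equivalent to 12 sessions". The control condition is standard hospital care, with rehabilitation if needed; no study sessions are described for it. Under Procedure, every participant passes through both conditions, in one of two orders.

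**The concern.** Improvement in fatigue, pain and breathlessness is the stated aim, so worsening of the same symptoms under training is the harm that a reader will look for first. As the safety section stands, worsening fatigue or breathlessness enters the adverse event record only if the participant volunteers it, unless it leads to hospital admission. A participant in training sees a trainer alone twice a week; a participant in the control period has no such occasion. A difference between conditions in reported worsening could then reflect contact rather than harm, and the absence of a difference would be equally hard to read. The results are meant to inform larger trials and rehabilitation guidelines, so an adverse event table that cannot be compared between conditions is a real weakness, although it does not touch the primary analysis.

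**Working it through.** The plan gives no figure on this point, so there is none to reproduce. The check sets the sections side by side.

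**1. Target symptoms against the adverse event list**

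| Symptom (Objectives) | Named as an adverse event? |
|---|---|
| Fatigue/tiredness | No |
| Musculoskeletal pain | Only if it prevents training |
| Shortness of breath | No |

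One of three is named, with a condition attached. That condition is inability to train, so the item has little application in a period without training.

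**2. Scheduled study sessions per 6-week period**

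- Exercise: 2 sessions per week × 6 weeks = 12, one-to-one, in either sequence.
- Control: 0 described, in either sequence.

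**3. Other contact between visits**

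The data collection section provides telephone contact between T1 and T2, for retention. It reaches Sequence 1 during exercise and Sequence 2 during control. The legend of Fig. 2 has Sequence 1 (n=50) begin without exercise: "Participants will be first randomly assigned to a 6-week period of no-exercise training". For that control period, T0 to T1, the only between-visit contact described is a reminder for overdue questionnaires. The T1 assessment then closes the period.

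**4. What the symmetric measurements can show**

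- *Medical interview and examination.* Listed under Outcome measures, which are assessed at T0, T1 and T2. Its content is not given.
- *Symptom questionnaire.* Given at baseline and at the end of each period. It is described as asking whether each symptom is present and whether it persists. For a symptom already present at entry, the answer is the same whether that symptom is unchanged or worse. The printed examples omit fatigue and breathlessness, but the list may not be exhaustive and the full instrument may hold graded items.
- *EQ-5D and its 0–100 visual analogue scale.* Graded and symmetric, so they can show decline, but they do not identify which symptom worsened or treat it as a harm.

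Nothing described says that an individual's answer to any of these is to be recorded as an adverse event.

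**5. Participants who leave**

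Missing values are replaced by the baseline value. Someone who stops because symptoms worsened, and misses the assessment, is analysed as unchanged on that outcome. The harm can then appear only in the spontaneous record or in the drop-out reasons, which monitors report where they see fit.

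**The case against.** The strongest reply is that worsening is already measured, as an outcome. Symptom change is an objective, all tests are two-sided, patient-reported outcomes are to be read by direction and size, and the safety section says that reports will include outcome comparisons between groups. Treating deterioration of a fluctuating target symptom as an outcome rather than an event is defensible and avoids double counting. Further, every period ends with an assessment that includes a medical interview, and the operations manual, record sheets and full questionnaire are not shown.

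Much of this stands, and it limits the point. A reader might infer that nobody asks about worsening in the control period. The article does not support that: the interview at T1 and T2 may well ask. Nor does it support the reading that such events cannot be recorded: open reporting admits them, and severe cases would appear as hospital admissions. A reader might also infer that exercise must look worse. More contact would push that way, but trainers or participants may regard symptoms as a normal effect of training, which would push the other way.

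What the reply does not remove is that group comparisons of outcomes do not count the individuals made worse. The questionnaire as described cannot show worsening of a symptom present at entry, and no stated route leads from these measurements to the adverse event record. The passive method and the four-item list are what the article itself states; they are not details left to another document.

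**Conclusion.** The point holds in a limited form. Worsening of fatigue and breathlessness is neither a named adverse event nor one that the article says will be asked about as such, and opportunity to volunteer it between visits is unequal: 12 sessions against none. Counts of symptom worsening as a harm may therefore not be comparable between conditions. That unequal contact leads to unequal reporting is an inference, though a reasonable one with unblinded participants. The direction is uncertain, and the article gives nothing from which to estimate the size or the number of participants affected; any ratio put on it would rest on assumed reporting rates. Coverage by the interview, questionnaire and EQ-5D is real but partial. This is a cheap improvement worth considering, held with medium confidence because unseen study documents may already provide it.

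**What to change.** In the safety section, add to the events recorded: *worsening of fatigue, breathlessness or other persistent COVID-19 symptoms, whether or not training is stopped*. Then:

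- Ask about it in identical words at the existing T1 and T2 assessments, in both conditions.
- Record the period in which it began, so that worsening that starts under exercise and lasts into control is counted under exercise.
- Report the number and proportion affected by condition, with the number asked as denominator.
- For participants without a T1 or T2 visit, use the drop-out reasons.
- Keep the open collection of spontaneous reports.

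If the interview, the questionnaire or the operations manual already asks this, one sentence saying so, and saying that the answers are reported as adverse events, is enough.

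The cost is one question at two existing visits, one line on the event form and one row in the safety table. Event counts will be higher. Recruitment began in March 2021 and was expected to be complete by September 2022, so participants who have already finished will lack the question and must be shown separately as not asked.
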